### 1 Executive Summary

Compromised respiratory function as a result of tetraplegia leads to many tetraplegics requiring mechanical ventilation during the acute phase of injury. Ventilation costs the local health care provider an additional £1000 per day per patient and reduces a patient's quality of life. Electrical stimulation of the abdominal muscles has previously been used to improve the respiratory function of tetraplegic patients in the chronic stage of injury. In this study we aim to evaluate whether electrical stimulation of the abdominal muscles can assist the process of weaning from mechanical ventilation in acute ventilator dependent spinal cord injured patients.

## 2 Introduction

Spinal cord injury can lead to paralysis of the limbs and muscles as well as a loss of function and sensation. When a person suffers an injury in the cervical (neck) region of the spinal cord, this is termed tetraplegia. Tetraplegia can lead to paralysis of all four limbs and affect the respiratory function of the patient. Poor respiratory function often leads to a patient with a cervical injury requiring mechanical ventilation and possibly a tracheostomy during the acute phase of injury [1].

Mechanical ventilation costs the local health care provider in the region of an additional £1000 per day for each patient [2]. Mechanical ventilation also reduces the patient's ability to take part in rehabilitation treatment which is a vital step of the recovery process [3]. If the time to wean from the ventilator can be reduced for this patient group this will result in a significant cost saving for the local health care provider, as well as greatly improving the patient's quality of life.

There are currently several methods available to promote weaning from mechanical ventilation. One traditional method to promote weaning is intermittent mandatory ventilation where the patient remains connected to the ventilator but is required to progressively initiate more breaths themselves. Spontaneous breathing trials (SBTs) have been shown to be a successful method to promote faster ventilator weaning than the traditional method of intermittent mandatory ventilation [4-6]. During SBTs the patient is encouraged to breathe on their own several times a day and the duration of this ventilator free time is progressively increased. As the amount of air which the patient can shift is likely to be very small at the initial stages of weaning, only short periods of time without ventilator support can be tolerated. However as the muscles regain strength the time without mechanical ventilation increases until eventually the patient becomes ventilator independent.

Functional Electrical Stimulation (FES) is a method of stimulating the motor nerves of a muscle using a small electrical current in order to gain a functional improvement. Functional electrical stimulation when applied to the abdominal muscles is termed Abdominal Functional Electrical Stimulation (AFES). AFES has been shown to increase tidal volume (amount of air in each breath) in tetraplegia [7,8]. AFES has also been shown to be a suitable approach to improve respiratory function in chronic ventilator dependent tetraplegics without spontaneous ventilation [9]. Recent studies have shown that AFES may be a suitable method to assist ventilator weaning in the ventilator dependent tetraplegic group [10]. By making use of AFES in the acute tetraplegic population, coupled with PVFB, it may be possible to improve tidal volume to such a degree that it reduces the patient's time on a mechanical ventilator.

The total time that each patient spends on mechanical ventilation varies significantly, and there are currently no clearly defined prediction methods for weaning times [11–13]. Some studies predict that injury level, age and sex are the best indicators of the time for which a patient is likely to be ventilator dependent. Therefore a possible approach for predicting weaning time is to match subjects with a retrospective control group based on injury level, age and sex.

In summary the use of AFES in acute ventilator dependent spinal cord injured patients could support faster weaning from mechanical ventilation, with the potential to reduce health care costs and significantly improve the patient's quality of life.

### **3 Aims**

The two main aims of this study are to evaluate the feasibility and effectiveness of abdominal Functional Electrical Stimulation to assist faster weaning from mechanical ventilation in acute ventilator dependent tetraplegic subjects.

Secondary aims of this study are (i) the evaluation of the engineering methods which have been developed to allow the synchronization of abdominal functional stimulation with a mechanical ventilator, and (ii) to investigate whether regular applications of abdominal functional electrical stimulation can improve the respiratory function of acute ventilator dependent tetraplegic patients.

### **4 Methods**

#### **4.1 Participants**

10 ventilator dependent tetraplegic participants in the acute stage of injury will be recruited while inpatients at the Queen Elizabeth National Spinal Injuries Unit (QENSIU), Southern General Hospital, Glasgow. The participants will then be matched for injury level, age ( $\pm 5$  years) and sex against a control obtained from records of previous patients in the QENSIU. The control data will be collected by [name] and the researchers will not have access to patient notes at any point during the study.

The participants will be recruited according to the following inclusion and exclusion criteria.

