While the participant is still not able to breathe independently of the ventilator, Phase 1 of Table 1, AFES will be applied while the participant is connected to the ventilator. However throughout Phase 1 the ventilator support will be reduced and the weaning process will begin. As weaning progresses, Phase 2,3 and 4 of Table 1, SBTs will begin and AFES will be applied with the participant disconnected from the ventilator. While the participant is off the ventilator their oxygen saturation level ( $\text{SaPO}_2$ ) will be monitored and recorded every minute. If the participant's  $\text{SaPO}_2$  level falls below 92% the participant will be immediately reconnected to the ventilator until the  $\text{SaPO}_2$  returns to the initial value. A previous study by Girard et al. [6] suggested a  $\text{SaPO}_2$  of 88% as the point at which heterogeneous participants in an ICU should be reventilated during SBTs. However inline with current clinical procedures at the QENSIU,  $\text{SaPO}_2$  of 92% was deemed a more appropriate level at which to reventilate the participant during this study.

The participant's weaning progress will be monitored throughout the course of the study. Three measures of ventilator weaning, adapted from a previous study by Narh et al. [11], will be used to determine whether weaning has been successful: The participant is (i) *awake weaned* when they are able to breathe independently of the ventilator during the day, (ii) *short term weaned* when they do not require ventilator for 24 hours, and (iii) *long term weaned* when they have been ventilator free for 7 days. Based on previous experience most participants will not need to be reventilated after short term weaning has been achieved, although this may be compromised by comorbidities such as respiratory infection. Weaning progress is recorded in the patient notes, allowing a comparison to be made between the participants and the historic control group.

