### **4.4 Outcome measures**

The main outcome measure of this investigation will be the time taken to wean from mechanical ventilation. Secondary outcome variables will be measures of respiratory function recorded throughout the intervention period.

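### Controls are matched from records that already hold the weaning outcome, with no rule for choosing among several eligible records and no masking of whoever chooses

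*Protocol*

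**What the plan says.** Section 4.1 sets the sample: "10 ventilator dependent tetraplegic participants in the acute stage of injury will be recruited while inpatients". It continues: "The participants will then be matched for injury level, age" (within 5 years either way) "and sex against a control obtained from records of previous patients in the QENSIU". The singular most naturally means one control per participant, although sections 2 and 4.2.1 speak of a control group. One named person collects the control data, and "the researchers will not have access to patient notes at any point during the study".

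Section 4.2.1 places the outcome in the same source: "Weaning progress is recorded in the patient notes, allowing a comparison to be made between the participants and the historic control group". Section 4.4 makes it the main one: "The main outcome measure of this investigation will be the time taken to wean from mechanical ventilation". Section 3 ranks effectiveness beside feasibility: "The two main aims of this study are to evaluate the feasibility and effectiveness of abdominal Functional Electrical Stimulation".

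The protocol gives no calendar period for the past patients, no count of eligible records, no rule for choosing among several, and no provision for a participant without a match. It does not say who makes the match or whether that person is masked to weaning time.

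**The concern.** A past patient's weaning time is fixed and on file before that patient is chosen as a control. If two or more records meet the matching criteria and the person choosing can see how each patient fared, the choice can follow the outcome. This needs no bad faith. Preferring the record that seems better documented or more comparable, after reading its course, is enough. The between-group comparison of weaning time rests on these controls, so bias in choosing them passes directly into the main result.

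There is a second, smaller loss. If several records qualify and one is used, the others are set aside although they would narrow the interval.

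**Working it through.** The protocol states no power, effect size or standard deviation (SD), so there is no figure of its own to reproduce. Section 2 says only that "The total time that each patient spends on mechanical ventilation varies significantly". The inputs are 10 participants (section 4.1) and an assumed number k of eligible records per participant, from 1 to 4 or 5.

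**Precision.** With k controls for each of 10 participants, equal variances and no correlation within sets, the standard error of the difference is SD × √(1/10 + 1/(10k)). Relative to one-to-one matching, the ratio is √((1 + 1/k)/2).

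| k | Standard error (SD units) | Ratio to 1:1 |
|---|---|---|
| 1 | 0.447 | 1.000 |
| 2 | 0.387 | 0.866 |
| 3 | 0.365 | 0.816 |
| 4 | 0.354 | 0.791 |

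With a common correlation ρ within sets, the standard error is SD × √((1 − ρ)(1 + 1/k)/10), so the ratios do not change. They do assume that every participant has k matches. If only half have two and the rest have one, the standard error is √((10 + 5 + 5/2)/100) = 0.418 SD, a ratio of 0.94.

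**Selection, in days.** Suppose weaning time is log-normal with median 40 days and log-SD s, and the slowest of k eligible records is always taken. The median of the chosen control is 40 × exp(s × z), where z is the standard normal quantile at 0.5^(1/k): 0, 0.545, 0.819 and 0.998 for k = 1 to 4. Neither the median nor s comes from the protocol, so s is varied.

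| k | s = 0.5 | s = 0.8 | s = 1.0 |
|---|---|---|---|
| 1 | 40 | 40 | 40 |
| 2 | 53 | 62 | 69 |
| 3 | 60 | 77 | 91 |
| 4 | 66 | 89 | 109 |

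The median of 40 only sets the scale. At s = 0.8 the multipliers for k = 2, 3 and 4 are 1.55, 1.93 and 2.22 whatever the true median.

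**Selection, in SD units.** This was a simulation of 50,000 trials with no true effect, 10 pairs, a normal outcome and a paired t-test at two-sided 0.05. With the slowest record always taken and no correlation within sets, the results were:

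| k | Spurious benefit (SD) | False significance favouring stimulation |
|---|---|---|
| 1 | 0 | about 2.5% |
| 2 | 0.57 | 23% |
| 3 | 0.85 | 48% |
| 4 | 1.03 | 66% |
| 5 | 1.16 | 78% |

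If outcome-driven choice affects only 25% of matches, the last column becomes 4.7% (k = 2) or 6.5% (k = 3). At 10% of matches it is 3.2% or 3.7%.

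**The case against.** A reader might infer that controls are chosen with weaning times in view, by the person who collects the data. The protocol says neither. The matching sentence is passive and names no one. If the researchers matched from a list of injury level, age and sex, the person choosing would never see an outcome. This part of the objection stands: the defect is that the choice is left unprotected, not that it is shown to be unblinded. The bar on researcher access is a real but partial safeguard, because it does nothing if the collector chooses.

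Matching after recruitment is not itself a fault, since a participant's injury level, age and sex are unknown before then.

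The pool may also be thin. Controls come from one unit and must agree on three characteristics, and section 4.5 ties the target number mainly to patient availability. One match or none is plausible, and with one match both effects are zero. It therefore cannot be said that precision is being wasted, only that it would be where several records qualify.

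Nor can it be said that selection could outweigh any plausible effect. The protocol defines no such effect and section 4.5 calls effectiveness largely unknown.

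Finally, a statistical analysis plan not seen here might set the matching ratio and a tie-breaking rule. But who forms the control group, and when, is a design step fixed in section 4.1. An analysis plan cannot repair a choice already made with outcomes known.

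**Conclusion.** The concern holds in conditional form. Section 4.1 draws controls from records that already contain the main outcome, with no rule among several eligible records and no masking of whoever selects. Where more than one record qualifies, this leaves room for outcome-influenced selection and discards usable controls.

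The precision part is a standard error at 87%, 82% or 79% of the one-to-one value with 2, 3 or 4 controls per participant, assuming equal variances and that number of matches for everyone. The selection part is an upper bound on assumed inputs: a 40-day median moving to about 62 to 89 days for k = 2 to 4 at log-SD 0.8. Partial selection would do much less. The documents give no means of telling how many records qualify. The change is worth making because it costs little and does no harm if the answer is one.

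**What to change.** Amend section 4.1 in four steps.

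1. List all ventilated past patients of the unit in a stated calendar period, showing only injury level, age, sex and the fact or start date of ventilation. Leave out weaning and end dates, because a start and end date together would reveal the duration that is to be hidden.
2. Fix each participant's matched set from that list before any weaning date is abstracted.
3. Use every eligible control in each set, weighted equally within the set.
4. State what is done when a participant has no match.

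The cost is some extra chart abstraction by the same person. No additional patients or procedures are needed.

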#### **Inclusion criteria:**

- Men or women over 16 years of age;
- Acute spinal cord injury (Patients with a new spinal cord injury);
- Reduced respiratory function requiring mechanical ventilation;
- Good visual response to surface abdominal stimulation, suggesting that lower motor neurons are intact.

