#### 4.2.2 Assessment sessions

An initial assessment session, represented by A0 on Figure 1, will be conducted on day 1 of the study to provide a baseline measure of the participant's respiratory function. Assessment sessions will then be conducted once per week to assess weaning progress as shown in Figure 1. The assessment sessions will be carried out in place of a regular weaning session, and may be augmented with a period of AFES training to ensure that the prescribed period of AFES is achieved (see above).

During the assessment sessions two breathing modes will be assessed.

1. *Unassisted breathing*: The participant will be asked to breathe without ventilator support. Tidal volume (amount of air inhaled and exhaled during a breath,  $V_T$ ) and vital capacity (total lung capacity,  $V_C$ ) will be measured. It is expected that while the participant is in Phase 1, 2 and 3 of weaning (Table 1),  $V_T$  and  $V_C$  will be similar. Once the participant moves onto Phase 4 the  $V_C$  will become larger than  $V_T$  as the participant begins to be able to breathe more efficiently.  $V_T$ , together with breathing rate, will be measured during normal ventilator free breathing. During Phase 4,  $V_C$  will be assessed by asking the participant to inhale to maximum volume and then fully exhale.

2. *AFES assisted breathing*: The participant will be asked to breathe on their own without the support of the ventilator, but with the assistance of abdominal FES. The same measurements as for unassisted breathing will be recorded.

Each of the breathing modes will be assessed for 6 minutes or until the participant's SaPO2 level drops below 92%. Both modes will be separated by a break of at least 2 minutes duration, or until the participants SaPO2 returns to the starting level. Participants will be ventilated during this break if required.

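### Historical controls need not be still ventilated at the participant's entry day and time to wean has no stated origin, so the main comparison is open to immortal-time or misaligned-origin bias

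*Protocol*

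**What the plan says.** Section 4.1 plans that "10 ventilator dependent tetraplegic participants in the acute stage of injury will be recruited while inpatients". Each is then matched on injury level, age within 5 years and "sex against a control obtained from records of previous patients in the QENSIU". Section 2 gives the reason for these three factors: "Therefore a possible approach for predicting weaning time is to match subjects with a retrospective control group based on injury level, age and sex". Time since injury and time since start of ventilation are not among them.

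To enter, a participant needs "Reduced respiratory function requiring mechanical ventilation" and "Acute spinal cord injury (Patients with a new spinal cord injury"; no limit is set on time since injury or on days already ventilated. Section 5.1 places certification of incapacity, the approach to the guardian or relative, and proxy consent before participation. The initial assessment, A0, "will be conducted on day 1 of the study to provide a baseline measure". Controls have no corresponding date.

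Section 4.4 states: "The main outcome measure of this investigation will be the time taken to wean from mechanical ventilation". Section 4.2.1 defines three end states (awake, short-term and long-term weaned) and plans a comparison with the historic controls from the patient notes, but no section says when the clock starts.

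**The concern.** A patient who weaned before certification, proxy consent and A0 were complete cannot be a participant. The same patient can be a control if level, age and sex match. Participants are therefore selected for not having weaned early and controls are not. What this does to the result depends on the clock, which is open.

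- **Both groups from start of ventilation.** Participants carry a period in which, by selection, they could not have weaned. This is immortal-time bias in the strict sense, and it makes AFES look worse.
- **Participants from A0, controls from start of ventilation.** The two times measure different things. The error may favour AFES, go against it, or vanish.

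Effectiveness is one of the two main aims in section 3, and weaning time is the main outcome. A difference of days to weeks could come from the choice of controls alone.

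**Working it through.** **Inputs from the protocol.** 10 participants; three matching factors; ventilation required at entry; no origin for the outcome. There is no stated sample size or power figure to reproduce: section 4.5 sets the number of patients by availability.

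**Inputs assumed.** The protocol gives neither weaning times nor entry delay. I take a median time on ventilation of 40 days, entry (A0) on day e = 7, 14 or 21 of ventilation, and no AFES effect. Four distributions cover a range of shapes: log-normal with log-SD 0.8 and 1.2, exponential, and Weibull with shape 2.

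**Formula.** Let S(e) be the probability of still being ventilated on day e. Participants are those with weaning time above e, so their median from start of ventilation, m(e), solves S(m) = S(e)/2. Their median from A0 is m(e) − e. Unselected controls have a median of 40 from start of ventilation.

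- Exponential: m(e) = 40 + e. For e = 21, m = 61; from A0, 61 − 21 = 40.
- Weibull, shape 2: m(e) = √(40² + e²). For e = 21, m = √(1600 + 441) = 45.2; from A0, 24.2.
- Log-normal, log-SD σ: S(e) = Φ(ln(40/e)/σ) and m(e) = 40·exp(σ·Φ⁻¹(1 − S(e)/2)). For σ = 0.8 and e = 14, S = Φ(1.312) = 0.905, Φ⁻¹(0.547) = 0.119, and m = 40·exp(0.095) = 44.0; from A0, 30.0.

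**Results**, in days, for entry on day 7 / 14 / 21; controls' median 40:

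| Distribution | Participants from start of ventilation | Difference | Participants from A0 | Difference |
|---|---|---|---|---|
| Log-normal, 0.8 | 40.6 / 44.0 / 49.5 | +0.6 / +4.0 / +9.5 | 33.6 / 30.0 / 28.5 | −6.4 / −10.0 / −11.5 |
| Log-normal, 1.2 | 44.7 / 53.5 / 63.1 | +4.7 / +13.5 / +23.1 | 37.7 / 39.5 / 42.1 | −2.3 / −0.5 / +2.1 |
| Exponential | 47 / 54 / 61 | +7 / +14 / +21 | 40 / 40 / 40 | 0 / 0 / 0 |
| Weibull, shape 2 | 40.6 / 42.4 / 45.2 | +0.6 / +2.4 / +5.2 | 33.6 / 28.4 / 24.2 | −6.4 / −11.6 / −15.8 |

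On the ventilation-start clock the difference is always against AFES, from about 1 to 23 days. On the mixed clock it runs from about 16 days in favour to about 2 days against.

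**False-positive rate, for illustration.** The protocol names no test. With an assumed paired t-test on log time, 10 pairs and a two-sided 5% level, the mixed clock at entry on day 14 to 21 gives 11 to 13% (log-normal, 0.8) and 17 to 30% (Weibull, shape 2), almost all as false benefit. It stays near 5% for exponential times and for log-normal times with log-SD 1.2.

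**Check of the remedy.** If controls must be still ventilated on day e and both clocks start there, both groups have the same distribution when AFES has no effect. In simulation the medians differ by no more than 0.2 days and the error rate is 4 to 5%. Both parts are needed: if controls are still ventilated on day e but counted from start of ventilation, while participants are counted from A0, participants look faster by the whole delay e.

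**The case against.** The strongest reply has four parts.

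1. **The clock belongs in the analysis plan.** That plan is not shown and may define the origin or use a delayed-entry analysis from start of ventilation, which would remove the bias. Section 4.1 also matches after recruitment, so the entry day is known when the control is chosen. A reader might infer that no analysis could repair the comparison; the protocol does not support that. What remains is that the matching set is fixed in the protocol and lacks the needed condition. The researchers have no access to patient notes, so whoever extracts control data needs the rule and the extra date beforehand.
2. **The bias is not certain under every clock.** A reader might infer bias whichever clock is used, or that counting from A0 always flatters AFES. Neither holds: the mixed-clock difference is zero for exponential times, changes sign for log-normal times with log-SD 1.2, and goes against AFES for a Weibull with shape 0.8 (46 to 51 days against 40). The protocol nowhere proposes a mixed clock. Section 2 speaks of total time on ventilation, which hints at the ventilation-start clock for both groups; with entry on day 7 the bias there can be under one day.
3. **This is a feasibility study.** Section 4.5 says so, no confirmatory test is stated, and the alternate on and off weeks in section 4.2.1 give a second, within-participant indication of effect. That is fair, and the error rates above do rest on an assumed test. But effectiveness is a main aim, weaning time is the main outcome, and section 4.2.1 plans the historic comparison. A small sample explains imprecision, not a systematic error.
4. **Controls were also patients of the unit.** Any selection by admission to it is therefore partly shared. This narrows the asymmetry but leaves the time from admission to A0, which the protocol does not bound.

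**Conclusion.** The point stands in this form: the stated control rule and the missing origin leave the main outcome comparison open to immortal-time or misaligned-origin bias. The direction is known only if both clocks start at ventilation, where it is against AFES. The range of about 1 to 23 days slower on that clock, and about 16 days faster to 2 days slower on the mixed clock, rests on an assumed median of 40 days, entry on day 7 to 21 and the four distributions shown; the protocol supplies none of these. It would go too far to say that the trial must show a difference when AFES does nothing. With a short entry delay, a suitable distribution or a delayed-entry analysis, the bias may be negligible. The protocol as written gives no assurance of any of these.

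**What to change.** - **Section 4.1:** add as a matching condition that the control was still ventilated on the same day since start of ventilation as the participant at A0. Apply to controls those eligibility criteria that can be checked in records.
- **Section 4.4:** start the clock for time to wean on that matched day in both groups.
- **Fallback:** if a participant has no such control, use a delayed-entry analysis from start of ventilation, in which the participant joins the risk set on the day of A0.
- **Limitation to state:** the criterion "Good visual response to surface abdominal stimulation, suggesting that lower motor neurons are intact" cannot be checked in past patients. It is a separate selection difference that this change does not remove.

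The cost is one sentence each in 4.1 and 4.4, one more date per control chart, and a smaller control pool. The protocol does not allow the reduction to be estimated, and in a single unit some participants may be left without a match, hence the fallback.

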#### **Exclusion criteria:**

- Under 16 years of age;
- Female subjects who are pregnant;
- Significant history of autonomic dysreflexia;
- No visual response to surface abdominal stimulation, suggesting that lower motor neurons are not intact.

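### Section 4.1 states its eligibility criteria for recruited participants only and selects historical controls on injury level, age and sex alone, so the groups compared on time to wean can differ in eligibility as well as treatment, with a bias of unknown direction and size.

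*Protocol*

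**What the plan says.** Section 4.1 plans ten participants ("10 ventilator dependent tetraplegic participants in the acute stage of injury will be recruited while inpatients"). On the controls it says "The participants will then be matched for injury level, age" (within 5 years) and sex, "against a control obtained from records of previous patients in the QENSIU". The same section continues: "The participants will be recruited according to the following inclusion and exclusion criteria".

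The inclusion list requires age over 16, a new spinal cord injury, respiratory function poor enough to need mechanical ventilation, and "Good visual response to surface abdominal stimulation, suggesting that lower motor neurons are intact". The exclusion list removes pregnant women, anyone with "Significant history of autonomic dysreflexia", and anyone with "No visual response to surface abdominal stimulation, suggesting that lower motor neurons are not intact".

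No section applies either list to the control records. Section 4.4 states: "The main outcome measure of this investigation will be the time taken to wean from mechanical ventilation". Section 4.2.1 says that weaning progress is taken from patient notes so that participants can be compared with the historic group. Section 3 makes effectiveness one of the two main aims.

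**The concern.** A historical comparison is open to any systematic difference between the groups other than treatment. Here one such difference is built into the selection rule. Every participant has passed a bedside stimulation test and a dysreflexia exclusion, while a control has only to agree on three matching variables. If patients who would fail those criteria have a different typical weaning time, the control group's mean shifts for a reason unrelated to AFES.

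The shift would be systematic. Recruiting more patients would not remove it, and a confidence interval would not reveal it. It would persist even if both groups shared the same starting point for counting time and the controls were chosen blind to outcome.

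This is not a matter that a protocol usually leaves to the analysis plan. Who qualifies as a control is a design rule set in 4.1, the records are collected under it, and a later analysis cannot easily repair a pool assembled under a looser rule.

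**Working it through.** The protocol gives no figure for this point, so there is none to reproduce. Section 4.5 sets the sample size by patient availability, without an effect size or variance.

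**Step 1: the criteria, group by group.**

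| Criterion in 4.1 | Participants | Controls |
|---|---|---|
| Injury level, age within 5 years, sex | basis of matching | matched |
| Age limit | required | not stated; largely covered by age matching |
| New injury | required | not stated |
| Mechanical ventilation | required | not stated; implied by having a time to wean |
| Not pregnant | required | not stated |
| No significant dysreflexia history | required | not stated |
| Good response to abdominal stimulation | required | not stated |

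The gaps that matter are the last two rows.

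**Step 2: does matching on injury level replace the screen?** The protocol does not treat it so. It tests stimulation response in each candidate and allows for both outcomes, so it expects lower-motor-neuron integrity to vary within the recruited population.

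**Step 3: does another comparison rescue the main outcome?** The alternating weeks with and without AFES (4.2.1) and the unassisted versus AFES-assisted breathing tests (4.2.2) are made within the patient and need no controls. Neither measures time to wean. A participant has one time to wean, so that outcome can be compared only between groups.

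**Step 4: how the sign depends on unknowns.** Suppose AFES has no effect. Let *q* be the share of controls who would fail the screen, and *r* their mean weaning time relative to patients who would pass. Then

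- control mean / participant mean = 1 + *q*(*r* − 1)
- apparent reduction with AFES = 1 − 1/[1 + *q*(*r* − 1)]

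Both *q* and *r* are assumptions; the protocol gives neither.

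| *r* | *q* = 0.1 | *q* = 0.3 |
|---|---|---|
| 0.8 | 1 − 1/0.98 = −2.0% | 1 − 1/0.94 = −6.4% |
| 1.0 | 0% | 0% |
| 1.25 | 1 − 1/1.025 = 2.4% | 1 − 1/1.075 = 7.0% |
| 2.0 | 1 − 1/1.1 = 9.1% | 1 − 1/1.3 = 23.1% |

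Negative values run against AFES. The assumed range of *r* reaches further above 1 than below it; that is a choice of inputs and not evidence about direction.

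**Step 5: could the mismatch easily be absent by chance?** Assume one control per participant, hence ten controls. The chance that at least one would have failed the screen is 1 − (1 − *q*)^10, which is 65% for *q* = 0.1, 89% for *q* = 0.2 and 97% for *q* = 0.3.

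**The case against.** The strongest reply has four parts.

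- **Silence is not exemption.** The protocol does not say that controls are free of the criteria, and several are implied in practice (see the table). This stands as a limit on the wording. It does not close the gap for stimulation response and dysreflexia, where nothing is implied.
- **The direction is undocumented.** A reader might infer that the screen removes slow weaners from the treated group and so flatters AFES. The documents do not support that. Section 2 names injury level, age and sex as the best indicators in some studies, and all three are matched. Nothing links lower-motor-neuron integrity to weaning time. Where the abdominal muscles are paralysed, an intact lower motor neuron makes them stimulable but does not by itself give voluntary force. This stands in full. On the other side, the protocol seeks faster weaning by strengthening these muscles, so a link is plausible, and section 2 also says that no clearly defined way of predicting weaning time exists.
- **The screen cannot be mirrored.** Stimulation response was presumably not tested in past patients, although the protocol does not say so. A checklist then removes only part of the difference. This stands. Excluding records with documented lower-motor-neuron damage to the abdominal muscles does not create a new asymmetry, because such a patient would be expected to fail the screen.
- **Proportion.** This is a ten-patient feasibility study, and random error may well exceed the bias. That lowers the weight of the point, but effectiveness is a main aim and the correction is cheap.

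**Conclusion.** The point holds as a difference in eligibility between the groups compared on the main outcome. Followed as written, section 4.1 yields a treated group selected on stimulation response and dysreflexia history, and a control group selected on neither.

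The direction and size of the bias are not known. The percentages above show only that the sign turns on whether *r* is above or below 1; they are not estimates. A reader might also be tempted to express the bias in ventilator days, or in money at the protocol's £1000 per ventilated day. The documents give neither the share of past patients who would fail the screen nor their difference in weaning time, so no such figure can be supported.

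Two further inferences go too far. The screen suggests intact lower motor neurons to the abdominal muscles and says nothing about the overall extent of injury. And it would be wrong to say that the trial holds no information on AFES apart from the controls: the within-patient comparisons exist, but do not address time to wean. The point is one that should be corrected; it does not prevent the study from running.

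**What to change.** In section 4.1, add a rule for control records:

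1. A record qualifies only if the patient met every participant criterion that can be read from the notes: age, new injury, mechanical ventilation, not pregnant, and no significant history of dysreflexia.
2. Records with documented lower-motor-neuron damage to the abdominal muscles are excluded, as a proxy for the stimulation screen.
3. The protocol states that stimulation response itself cannot be fully mirrored in past records, so the control comparison carries a residual selection bias of unknown direction. The report repeats this limit.
4. The number of current candidates who fail the screen is reported as context only. It estimates neither the corresponding share among past patients nor their weaning time, and should not be used to correct the result.

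The cost is a short checklist for the person already extracting control records, a screening tally, and a slightly smaller pool of records. No procedure on participants changes.
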